## Administrative information

**Table Taba:** 

**Trial synopsis**	
**Title**	Axial ablation versus terminal interruption of the Reflux Source in venous ulcer management: a randomised controlled trial in venous ulcer management
**Public title**	AAVTIRS trial
**Medical condition under investigation**	Lower limb venous ulcers
**Purpose of trial**	To evaluate whether there is a clinically significant difference between axial ablation of varicose veins and peri-ulcer terminal interruption of the reflux source in promoting healing of lower limb venous ulcers.
**Primary objective**	To determine if the proportion of ulcers healed within 6 months of endovenous treatment differs between patients undergoing axial ablation of varicose veins or terminal interruption of the reflux source by peri-ulcer foam sclerotherapy.
**Secondary objectives**	To determine whether there is a significant advantage to either treatment, in a reduction in ulcer size, encouraging wound regeneration, and venous disease severity or a significant difference in patient-assessed quality of life, between the two interventions
**Trial design**	Prospective single-centre assessor-blinded randomised controlled trial
**Primary endpoint**	Proportion of ulcers healed within 6 months of intervention
**Secondary endpoints**	Absolute and relative reduction in ulcer size Time to ulcer healing BWAT score progression VCSS progression over time Change in Charing Cross Venous Ulcer Questionnaire score from treatment to completion of follow-up
**Sample size**	320 individual ulcers
**Summary of eligibility**	Patients with a leg ulcer, attributable to venous insufficiency, without any contraindication to compression or either of the comparator treatment modalities will be included.
**Screening process**	All patients with a venous ulcer attending a Leg Ulcer Centre Ireland—a dedicated venous ulcer assessment clinic in Roscommon University Hospital will be considered for enrolment.
**Randomisation**	Affected legs will be randomised in a 1:1 ratio to axial ablation or terminal interruption of the reflux source.
**Treatment**	Patients will be treated on the same day as randomisation according to their assignment to either group
**Follow-up**	Patients will be followed monthly for 6 months.
**End-of-study**	The trial will end when all patients have been enrolled and completed both treatment and 6-month follow-up.

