**Safety monitoring**	The principal investigator will be notified of any serious adverse events, and they will liaise with all investigators and the ethics committee.
**Criteria for stopping trial on safety grounds**	Unacceptable risk to participants due to unexpected serious adverse events Unacceptable rate of adverse events Interim demonstration of a significant difference in efficacy Interim demonstration of a significant difference in the rate of adverse or serious adverse events Intolerable discomfort during treatment or compression, or inability to adhere to the protocol for any other safety-related reason leading to insufficient compliance with randomisation
**Registration**	ClinicalTrials.gov registration NCT04484168. Registered on 23/7/2020
**Recruitment**	Commenced on 21 July 20—ongoing. Planned completion 1st quarter of 2022, last patient last visit 3rd quarter of 2022
**Recruiting country**	Ireland
**IPD sharing**	Not planned
**Funding**	No funding has been received for this research.
**Ethics**	Approved by the Galway University Hospitals Clinical Research Ethics Committee 18 June 2020, ref. no. C.A. 2416

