### Sample size

Power calculation [25] was informed by existing evidence [11–13, 15], predominantly the EVRA trial [15]. EVRA showed a 95% success rate for ulcer healing at 24 weeks. We anticipated a more modest success rate because our exclusion criteria did not limit participants to those with new ulcers. In addition, TIRS has very limited existing evidence with reporting healing ranging from 83 to 100% [21, 23]. An 80% success rate was felt to be reasonable for both treatments in a non-inferiority trial. A cohort of 308 patients (154 per arm) was required to ensure that if the null hypothesis should be rejected, the limits of a two-sided 90% confidence interval would exclude a difference between the groups of more than 15%, with 90% power at 5% significance level.

Given that existing evidence for TIRS consists mainly of small case series with widely varying healing rates, we planned once the first 50 cases exited the trial (either healed or completed 6 months of follow-up) as a pilot to inform a further power calculation for both superiority and non-inferiority outcomes.

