### Statistical analysis

Statistical analysis will be performed using StatsDirect Statistical Package version 3 (StatsDirect Ltd., Cambridge, UK.). All analyses will be performed on an intention-to-treat basis, but a per-protocol analysis will also be performed. Continuous variables will be presented as mean (± standard deviation) or median (± interquartile range) based on distribution, with 95% confidence intervals. They will be analysed using Student’s *T*-test for parametric and Mann-Whitney *U* test for non-parametric data. Categorical variables will be described in absolute numbers with percentage frequencies. The chi-squared and Fisher’s exact test will be used.

Trial allocation will be concealed during interim statistical analysis unless a significant difference is found at this point which warrants stopping of the trial or the interim analysis indicates the trial could not be completed within a reasonable timeframe.

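### The protocol permits an efficacy stop at the look after about 50 exits but sets no level or boundary, so the risk of a false claim of difference is uncontrolled (about 5.5% to 10% if read at 5%)

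*Protocol article*

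**What the plan says.** The look is described in two ways.

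- **Sample size section (protocol article).** Once 50 cases have healed or completed six months, their data serve as a pilot for a further power calculation, covering both superiority and non-inferiority. No efficacy stop is mentioned here.
- **Statistical analysis section.** Allocation stays concealed at the interim analysis "unless a significant difference is found at this point which warrants stopping of the trial", or unless the trial proves too long to complete.
- **Trial synopsis (stopping on safety grounds) and Criteria for discontinuation.** Both list "Interim demonstration of a significant difference in efficacy".

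None of these places gives a significance level, a boundary or an adjusted final level. The only testing level in the article belongs to the sample-size calculation, "with 90% power at 5% significance level", where it accompanies the aim that "the limits of a two-sided 90% confidence interval would exclude a difference between the groups of more than 15" percent. For categorical data the Statistical analysis section names the chi-squared test and Fisher's exact test, without saying which applies where. Under Trial monitoring, no independent data monitoring committee exists; interim results go to members of the vascular department who are not involved in running the trial.

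**The concern.** An interim efficacy comparison that can end the trial is an extra chance to declare a difference. Unless its threshold is strict or the final level is adjusted, the chance of wrongly declaring one treatment better exceeds the nominal level. Here the threshold is not merely left for later detail: the protocol itself fixes the trigger, in three places, as a significant difference, and stops there.

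Two things are at stake.

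- **Practice.** The abstract's discussion says that a finding in favour of axial ablation would suggest full treatment of superficial reflux for all patients having ablation for venous ulcers. A false difference would therefore carry weight.
- **The primary question.** The Aim and the primary objective ask about equivalence. A stop after about 50 ulcers would leave that unanswered.

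**Working it through.** **Inputs from the protocol**
- Healing: 80% in both arms ("An 80% success rate was felt to be reasonable for both treatments in a non-inferiority trial").
- Margin: 15 percentage points ("exclude a difference between the groups of more than 15" percent).
- Size: "A cohort of 308 patients (154 per arm) was required"; the synopsis has "320 individual ulcers".
- Allocation 1:1; look after 50 exits.

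**Assumptions**
- 25 ulcers per arm at the look, from the 1:1 ratio.
- Two-sided 5% at both looks. The protocol states 5% for the sample size, not for the interim.
- Every crossing at the interim stops the trial.

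**1. The plan's own figure.** Equivalence formula (two one-sided tests): n per arm = 2p(1−p)(z₀.₉₅ + z₀.₉₅)² / margin². The second z is z₁₋β⁄₂ with β = 0.10.

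2 × 0.8 × 0.2 × (1.645 + 1.645)² / 0.15² = 153.9, so 154 per arm and 308 in total. The stated size is reproduced.

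**2. Timing.** 50/308 = 0.162 and 50/320 = 0.156.

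**3. Two looks, normal theory.** With no true difference, the two test statistics are bivariate normal with correlation √(50/308) = 0.403 (√(50/320) = 0.395 for 320). The probability that |Z| > 1.96 at either look is 9.3% for both sizes, against 5% for a single look.

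**4. Two looks, exact binomial enumeration** (25 then 154 per arm, 80% healing in both arms):

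| Test at interim / final | Interim alone | Final alone | Either look |
|---|---|---|---|
| Chi-squared (uncorrected) / chi-squared | 5.5% | 5.1% | 9.9% |
| Fisher / chi-squared | 2.2% | 5.1% | 7.0% |
| Fisher / Fisher | 2.2% | 3.5% | 5.5% |

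Relative to the single final look, the ratios are 9.9/5.1 = 1.9, 7.0/5.1 = 1.4 and 5.5/3.5 = 1.6. At 60% to 70% healing the overall rate is 9.7% to 10.4% with chi-squared at both looks and 5.8% to 6.5% with Fisher at both.

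**5. Size of difference that would cross at the interim.** With 20/25 healed in one arm:
- 13/25 in the other (28 points): chi-squared p = 0.037, Fisher p = 0.072.
- 12/25 in the other (32 points): Fisher p = 0.038.

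The observed difference needed is thus 28 points with chi-squared and 32 with Fisher, about twice the 15-point margin.

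**6. Effect of a strict boundary.** With two-sided p<0.001 at the interim and 5% at the end, the normal-theory calculation in step 3 gives an overall rate of 5.07%.

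**The case against.** - **The interim level is not stated.** The 5% belongs to the sample-size calculation, and a boundary could sit in an analysis plan that is not shown. The first part stands, so the 5%-plus-5% calculation illustrates one reading of the rule. The second does not remove the point: the protocol states the stopping trigger itself and leaves its threshold undefined.
- **The inflation depends on the test.** A reader might infer that the false-positive rate nearly doubles. That holds for chi-squared at both looks. Fisher is also named, and with only about 5 unhealed ulcers expected per arm (25 × 0.2) it is a realistic choice at the interim. It is conservative, and with Fisher throughout the overall rate is close to 5%. This stands, and a range is the fair summary.
- **Significance alone does not force a stop.** A reader might infer that any significant difference ends the trial. The wording requires one that warrants stopping, and the discontinuation section asks for reasonable justification. The figures are therefore upper bounds for each choice of tests. Unspecified judgement does not, however, control the error.
- **The primary error is false equivalence.** The Aim makes a clinically significant difference the null hypothesis, and stopping for a difference cannot add false equivalence claims. This stands; the inflated error is that of a superiority-type claim, which the abstract's discussion and the Sample size section both contemplate.
- **The safety heading in the synopsis.** A reader might infer that the efficacy rule would be applied loosely because it is listed there. The document does not support this: the same criterion appears under the general discontinuation criteria.

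**Conclusion.** The point holds as a stopping rule that is stated but badly fixed. Efficacy stopping is permitted at about 16% of the planned size with no threshold, at a look that the Sample size section describes only as a pilot.

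Read at 5% at both looks, with every crossing leading to a stop and 80% healing in both arms, the chance of a false claim of difference is at most about 5.5% to 10%, depending on which of the two named tests is used at each look. It rests on the assumed interim level and on 25 ulcers per arm. Whichever test is chosen, the second look raises the rate above that of the final analysis alone.

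**What to change.** Before any interim comparison by arm is made, do one of the following.

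1. **Remove the efficacy stop** at the 50-exit look from the synopsis, the Statistical analysis section and the Criteria for discontinuation. Use the look only for sample-size re-estimation on pooled data and for safety.
2. **Replace the words about a significant difference** in those three places with one stated strict boundary and a named test, for example two-sided p<0.001. Other strict boundaries would also serve, provided that the final level is set to match.

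Under either option, make the Sample size section describe the purpose of the look in the same way as the other three places.

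The cost is wording only, and the planned size does not change. With p<0.001 the final 5% level can stay, since the overall rate is about 5.1%. The downside is a smaller chance of stopping early if one treatment really is much better.

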### Criteria for discontinuation

Should reasonable justification for termination or suspension of the trial be encountered the principal investigator will notify the regional research ethics committee and all investigators involved in the trial in writing.Unacceptable risk to participants due to unexpected significant adverse eventsInterim demonstration of a significant difference in efficacyInterim power calculation indicating that significantly more participants would be required, which would prevent the trial being completed within a reasonable timeframeIntolerable discomfort during treatment or compression, or inability to adhere to protocol for any other reason leading to insufficient compliance with randomisationIncomplete data collection precluding coherent analysis

### Protocol violations

Inability to tolerate AA or TIRS, or compression bandages will constitute a violation of protocol. Failure to attend follow-up on a single occasion will not constitute a protocol violation, and patients will be contacted by phone to arrange further follow-up. All analyses will be performed primarily on an intention-to-treat basis, but a per-protocol analysis will also be performed.

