## Aim

The aim of this trial is to answer the following research question.

In adult patients with venous ulcers, are TIRS and AA equivalent in their ability to increase the proportion of ulcers that heal completely within 6 months of treatment?

Null hypothesis: there is a clinically significant difference in ulcer healing.

Alternative hypothesis: there is no clinically significant difference in ulcer healing.

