### Method of blinding

The trial will be assessor blinded. The trial nurse(s) will assess all wounds prior to randomisation and will be blinded to treatment allocation throughout, performing assessments at each follow-up visit. Patients will be instructed not to reveal the nature of their treatment in follow-up. The operation note from the intervention will be filed in the patient notes to allow intentional or emergency access. All members of the trial team involved in data collection and analysis will not be present when the envelope is opened at the time of treatment.

Any treatment decisions required beyond the trial protocol will be made by a member of the surgical team who is already unblinded.

Ultrasound assessment of treated veins will be avoided unless otherwise indicated, to minimise risk of inadvertent unblinding of assessors.

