#### AA

I.Ultrasound guided micropuncture of the desired axial veinII.Placement of a 5 French-gauge sheathIII.Passage of the Clarivein™ device to the proximal end of the treatment areaIV.Activation of the device, followed by withdrawal at a rate of 1 mm/s, while simultaneously infusing Sotradecol.

Variations of these treatments are at the discretion of the treating surgeon as long as the above steps are met. After treatment, all patients will be placed in compression bandages. They will then be followed up monthly at the same site with changes of their compression bandages in between by their local public health nurse (PHN) weekly, or more frequently as needed. If at any follow-up visit, their ulcer is seen to have healed, the time at which it healed will be noted in weeks from intervention. At this point, they will have completed their follow-up and will exit the trial. Patients in whom the ulcer has not fully healed at 24 weeks will also exit the trial. In either case subsequent treatment will be at the discretion of the surgical team.

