#### Drop-out criteria

Participants will be considered to have left the study if, despite all efforts of the trial team, no reliable determination can be made regarding the primary outcome.

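### For an equivalence aim, intention-to-treat alone leads, the named violations omit receipt of the other procedure, and undetermined outcomes are not reconciled with intention-to-treat

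*Protocol article*

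**What the plan says.** The Aim section asks "are TIRS and AA equivalent in their ability to increase the proportion of ulcers that heal completely within 6 months of treatment", and the primary objective is also framed as equivalence. The Sample size section assumes 80% healing in both arms and 154 per arm, so that "the limits of a two-sided 90% confidence interval would exclude a difference between the groups of more than 15" percentage points. That section also uses the term non-inferiority: "An 80% success rate was felt to be reasonable for both treatments in a non-inferiority trial".

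On analysis sets, the Protocol violations section says: "All analyses will be performed primarily on an intention-to-treat basis, but a per-protocol analysis will also be performed". The Statistical analysis section says much the same. Neither gives per-protocol equal standing or says what follows if the two sets disagree.

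On violations, the protocol states that "Inability to tolerate AA or TIRS, or compression bandages will constitute a violation of protocol", and that one missed visit is not a violation. Receipt of the other arm's procedure is not mentioned. Two other places leave room for mixed treatment. The AA section says "Variations of these treatments are at the discretion of the treating surgeon as long as the above steps are met". The Method of blinding section says "Any treatment decisions required beyond the trial protocol will be made by a member of the surgical team who is already unblinded".

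On missing outcomes, the Drop-out criteria section treats participants as having left the study if "no reliable determination can be made regarding the primary outcome". Ulcers seen to be healed at a visit exit the trial at that visit.

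**The concern.** In a superiority trial, intention-to-treat is the cautious choice, because switching shrinks the difference and works against the claim. In an equivalence trial the same shrinkage works for the claim. A per-protocol analysis is the usual counterweight, but only if it bears on the conclusion and its definition catches the deviation that matters. Here per-protocol is supplementary, and the listed violations catch intolerance but not a leg that received the other procedure for another reason, such as a surgeon's decision on the day. An AA leg that also had peri-ulcer foam would meet the listed AA steps and could look compliant.

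The drop-out wording raises a second problem. Because healed ulcers leave as successes, losses come from ulcers not yet recorded as healed. If those were left out of the denominator, healing would tend to be overstated, and the difference between arms would be biased if loss were unequal. At stake is whether an equivalence result reflects equal treatments or mixed treatment and selective loss.

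**Working it through.** **1. The plan's own figure.** Inputs from the Sample size section: 80% in both arms, 15-point margin, two-sided 90% interval (z = 1.645), 90% power (5% of the error on each side, z = 1.645).

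n = 2 × 0.8 × 0.2 × (1.645 + 1.645)² / 0.15² = 153.9, so 154 per arm, as stated. Exact binomial enumeration of the 90% Wald interval rule gives 90.1% power. A one-sided non-inferiority calculation at 5% and 90% power would give 122 per arm. The stated number is therefore an equivalence number.

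**2. Switching at the procedure, under intention-to-treat.** Assumed true healing is 80% (AA) and 65% (TIRS), exactly at the margin. A proportion c of TIRS ulcers receives AA instead and heals at the AA rate. The intention-to-treat TIRS rate is 0.65 + 0.15c, and the difference is d = 0.15 − 0.15c. The chance of claiming equivalence is approximately Φ((0.15 − d)/SE − 1.645). For c = 0.20: SE = √(0.8×0.2/154 + 0.68×0.32/154) = 0.0495, so Φ(0.03/0.0495 − 1.645) = 14.9%.

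| Switching TIRS to AA | TIRS rate | Difference | Normal approx. | Exact |
|---|---|---|---|---|
| 0% | 65.0% | 15.0 | 5.0% | 5.0% |
| 5% | 65.75% | 14.25 | 6.7% | 6.8% |
| 10% | 66.5% | 13.5 | 8.9% | 9.0% |
| 20% | 68.0% | 12.0 | 14.9% | 15.0% |

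If the same proportions also switch from AA to TIRS, the exact figures are 9.0%, 14.8% and 32.5%.

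**3. Adding a per-protocol set based on the index procedure.** Dropping the switched ulcers leaves 146, 139 or 123 in the TIRS arm. If switchers have the same prognosis as the rest, the difference returns to 15 points. Simulating both sets together gives a false claim in about 5% of trials at each switching rate. The price when both treatments truly heal 80%: for 154 v 123, SE = √(0.16/154 + 0.16/123) = 0.0484, and per-protocol power is 2Φ(0.15/0.0484 − 1.645) − 1 = 85.5%. By simulation, the chance that both sets succeed is about 88%, 87% and 84% at 5%, 10% and 20% switching.

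**4. Why per-protocol should not exclude later procedures.** Suppose 20% or 50% of the unhealed TIRS ulcers later have another venous procedure and those legs are excluded. Only failures are removed: 0.65/(1 − 0.35×0.2) = 69.9%, or 0.65/(1 − 0.35×0.5) = 78.8%. Against 80%, the deficit looks like 10.1 or 1.2 points, and false equivalence in that set is about 25% or 84%. Such a definition would make matters worse.

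**5. Undetermined outcomes.** These are illustrations of a complete-case reading:
- True healing 80% in both arms, 12% v 4% lost, 30% of those lost would have healed: (0.8 − 0.12×0.3)/0.88 = 86.8% v (0.8 − 0.04×0.3)/0.96 = 82.1%, a spurious 4.7 points. This makes equivalence harder to show.
- True 80% v 65%, 10% of TIRS ulcers lost, all unhealed (an extreme case): 0.65/0.90 = 72.2%, so a 15-point deficit looks like 7.8 points. This makes equivalence easier to show.

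**The case against.** Much can be said for the protocol. A per-protocol analysis is promised in two places. Treatment is a single procedure, given on the day of allocation where possible, with the envelope opened in the operating room, so switching may be rare. Missed visits are followed up by phone. Exact set definitions and missing-data rules often belong in an analysis plan, which is not shown. These points stand, and they limit the likely size of the problem. They do not change the stated rule that intention-to-treat leads for an equivalence question.

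Four stronger readings are tempting but not supported:
- *Cross-over ulcers stay in the per-protocol set.* The protocol never defines that set and does not call its list of violations exhaustive. A leg switched because of intolerance would be a violation as written.
- *Drop-outs are removed from the denominator.* The drop-out section says only that they have left the study. Complete-case is one possible reading.
- *Only unhealed ulcers can be lost.* Exit occurs at monthly visits, so an ulcer that healed between visits could also be lost.
- *Re-treatment of failures would drive the error very high.* If 20% or 50% of unhealed TIRS ulcers are ablated again and half then heal, false equivalence under intention-to-treat is about 17% or 57%. That re-treats one arm only. Applying the same rule to AA gives 82% v 68.5% and 85% v 73.75%, and about 9% or 21%. No passage suggests re-treatment at such rates.

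**Conclusion.** The concern holds in a limited form. For an equivalence aim and an equivalence sample size, the protocol makes intention-to-treat the sole lead analysis, gives per-protocol no say in the conclusion, and lists violations that omit receipt of the non-allocated procedure. With one-way switching of 5% to 20%, the chance of a false equivalence claim at the margin rises from 5% to between 6.8% and 15.0%. This rests on assumed rates of 80% and 65%, 154 per arm, and switched ulcers healing at the AA rate. The drop-out wording needs to be reconciled with intention-to-treat; the size and direction of any bias depend on loss rates that the protocol does not give. It would go too far to say that the planned sets give no protection.

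**What to change.** 1. Declare equivalence only if the 90% interval lies within ±15 points in both the intention-to-treat and the per-protocol sets.
2. Define per-protocol by the procedure actually received at the index treatment, and name receipt of the non-allocated or an additional procedure at that time as a deviation. Do not exclude legs for later procedures given because the ulcer had not healed. Record those procedures, and count such ulcers as unhealed on the allocated treatment in a sensitivity analysis.
3. Reconcile the drop-out criterion with intention-to-treat: keep all randomised ulcers in the denominator, count undetermined ulcers as unhealed, and vary that assumption by arm in a sensitivity analysis. The last step is needed because counting losses as failures can itself shrink a difference. For example, 10% loss unrelated to outcome in both arms turns 80% v 65% into 72% v 58.5%, or 13.5 points.

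The cost is a few sentences and the recording of later venous procedures. Requiring both sets lowers the chance of declaring equivalence, from about 90% to about 88% at 5% switching and 84% at 20%. Per-protocol also gives up some of the protection of randomisation, which is why it should stand beside intention-to-treat and not replace it.
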